### Run-in period and randomization

All eligible participants complete a run-in period where they are required to complete five separate visits prior to randomization. These visits include: 1) a baseline assessment with a peripheral venous blood sample; 2) three urine screening visits (regardless of the toxicology results) at the community-based CM program; and 3) a separately scheduled randomization visit where the first intervention or attention-control session is administered. Participants who fail to complete the run-in period are not randomized and do not complete subsequent visits for this RCT unless at some point they re-initiate contact with the study team and choose to be re-screened. Randomization is accomplished using a computer generated sequence with randomly permuted block sizes of 2, 4, and 6 to guard against subversion. Only the study data manager has access to the computer-based randomization algorithm. Because randomization occurs at the first intervention or attention-control session, this ensures that all participants in this RCT complete at least one of the five individually delivered sessions.

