### Outcome analyses

We will first generate one-way frequency tables for all variables and measures of central tendency and variability for continuous variables (e.g., means, medians, standard deviations) to perform range checks, quantify the amount of missing data, and yield valuable descriptive findings. Chi-square tests, *t*-tests, and comparable two-group non-parametric tests will be used to investigate equality of potential confounders (e.g., homelessness) across the intervention and attention-control conditions at baseline. Similarly, we will confirm that there are no differences in the mean number of intervention and attention-control sessions completed as well as no differential attrition by study arm.

Based on our extensive experience working with this population, we anticipate a maximum of 20% attrition over the 15-month investigation period. Attrition analyses will compare respondents who complete all measurements to those who do not based on baseline characteristics and we will test for differential attrition by intervention condition. Direct maximum likelihood and multiple imputation will be used to address incomplete data because these methods make the relatively mild assumption that missing data arise from a conditionally missing-at-random process [60].

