Intent-to-treat analyses will be conducted primarily using multilevel random coefficient models (i.e., hierarchical linear modeling; HLM). These models incorporate random intercepts and slopes for each participant based on the participant’s multiple measurements over time [61]. Initial models will be unadjusted and compare outcome trajectories for participants in ARTEMIS + CM and Attention-Control + CM across time via the group-by-time interaction effect. If preliminary analyses detect imbalance in potential confounders across the groups that cannot be satisfactorily addressed via covariate adjustment, we will substitute causal inference methods based on the Rubin causal model (e.g., propensity score weighting; marginal structural models) to obtain population-level effects of the intervention under the assumption of balanced confounders between the two groups [62–66]. A priori planned comparisons will be performed to test group differences at 3, 6, 12, and 15 months for both the primary and secondary outcomes. These planned comparisons will be evaluated at α = .05; any subsequent post-hoc comparisons will be adjusted via simulation-based stepdown methods to maintain a nominal Type I error rate of .05 [67].

The primary outcome will be log_10_ HIV viral load over the 15-month follow-up. Sustained HIV viral suppression will be examined as a secondary outcome using logistic regression of the binary outcome of sustained virologic suppression over the 15-month follow-up (0 = no; 1 = yes) on randomization group assignment. Other continuous secondary outcomes that will be examined in intent-to-treat analyses include: CD4+ T-cell count, positive and negative affect, stimulant craving, and self-reported stimulant use. Ordered categorical and categorical outcomes assessed repeatedly over the 15-month follow-up include: ART adherence and persistence, a positive urine toxicology result for stimulants, potentially amplified transmission risk partners stratified by methamphetamine use, and any potentially amplified transmission risk.

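### Weighting may replace the randomized comparison when baseline imbalance is judged not adequately handled by adjustment, so the primary estimate is not fixed in advance

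*Protocol article*

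**What the plan says.** All but the allocation method comes from the Outcome analyses section of the protocol article.

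- **Balance tests.** After naming the chi-square test and the t-test, the article adds: "comparable two-group non-parametric tests will be used to investigate equality of potential confounders (e.g., homelessness) across the intervention and attention-control conditions at baseline". No significance threshold is given for them.
- **Starting model.** Multilevel random coefficient models, of which the article says: "Initial models will be unadjusted and compare outcome trajectories for participants in ARTEMIS + CM and Attention-Control + CM across time". The arms are compared through the group-by-time interaction.
- **Rule for imbalance.** The rule, which starts from preliminary analyses, reads in part: "imbalance in potential confounders across the groups that cannot be satisfactorily addressed via covariate adjustment, we will substitute causal inference methods". Two examples are offered, propensity weighting and marginal structural models. The declared aim is an effect estimate under assumed balance of confounders.
- **Allocation** (Run-in period and randomization). "Randomization is accomplished using a computer generated sequence with randomly permuted block sizes of 2, 4, and 6", with the algorithm accessible only to the data manager.

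The article does not say that any one of the unadjusted, adjusted or weighted analyses remains primary.

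**The concern.** The rule treats a randomized trial as if it might need rescue from confounding. If the allocation worked, every baseline difference between arms arose by chance. A test of equality then asks a question whose answer is already known. Its p-value also says nothing about prognostic importance: a covariate unrelated to viral load can be flagged while one that predicts it strongly is not.

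The larger difficulty is what follows a flag. Three estimators are in play, and the step from the second to the third depends on whether adjustment is thought good enough. As the article orders the work, that view can be formed with the unadjusted and adjusted outcome results on the table. The verb in the rule is *substitute*, so the weighted estimate would displace the randomized comparison instead of standing beside it. At stake is which number the trial reports as its result for log10 viral load, and whether a reader can be sure that the choice did not depend on the answer.

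**Working it through.** **1. The rule, step by step.** The baseline tests are the only between-arm balance analyses described, so I take them to be the preliminary analyses that the rule refers to. Substitution then needs two things: (a) an imbalance is detected, and (b) covariate adjustment is judged not to deal with it. Step (a) uses baseline data only. Step (b) is a judgement, and nothing in the text places it before the outcome models are fitted.

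**2. The plan's own figure.** The article gives no number for this rule. Its Power analysis section supplies the sample size used below: 150 participants at 80% retention is 120, or 60 per arm if allocation is 1:1 (not stated). With two-sided 0.05, 80% power (assumed) and the mean of four equally correlated measures:

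d = (1.960 + 0.842) × √(2/60) × √((1 + 3ρ)/4) = 0.5115 × √((1 + 3ρ)/4)

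- ρ = 0.1: 0.5115 × √0.325 = 0.292
- ρ = 0.8: 0.5115 × √0.85 = 0.472

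The stated range of 0.29 to 0.47 is reproduced. The present point does not call that range into question.

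**3. Chance of passing step (a) under sound randomization.** For k independent tests at an assumed 0.05, the chance of at least one significant result is 1 − 0.95^k:

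| k | Chance of at least one flag |
|---|---|
| 1 | 5.0% |
| 5 | 22.6% |
| 10 | 40.1% |
| 15 | 53.7% |
| 20 | 64.2% |

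The number of covariates is not stated (homelessness is the only example), nor is the threshold, and real covariates are correlated. These are chances of step (a), not of substitution.

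**4. Effect on type I error.** I simulated a null trial with 60 per arm, one normal outcome, and k independent normal covariates that together explain 10% or 30% of its variance, with 6,000 runs per setting. When any covariate was flagged, the flagged ones were adjusted for or used in inverse-probability weights. Otherwise the unadjusted result stood.

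| k | Variance explained | Flagged | Adjust if flagged | Weight if flagged | Best of three | Best of three, flagged trials only |
|---|---|---|---|---|---|---|
| 5 | 10% | 22.6% | 0.047 | 0.047 | 0.052 | 0.080 |
| 5 | 30% | 22.6% | 0.046 | 0.046 | 0.058 | 0.103 |
| 10 | 10% | 39.4% | 0.047 | 0.047 | 0.055 | 0.077 |
| 10 | 30% | 40.2% | 0.038 | 0.039 | 0.053 | 0.076 |

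A switch applied mechanically stays at or below 5%. Inflation appears only if the most favourable of the unadjusted, adjusted and weighted results is taken. It is then small overall and larger among flagged trials. The simulation is a single-outcome simplification of the planned random coefficient model.

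**The case against.** The strongest reply is that this is a journal article. A covariate list, a threshold for imbalance and a criterion for adequate adjustment are commonly left to the full protocol or SAP, so their absence is no fault. That stands, and the point does not rest on it. It rests on what the article does commit to, which is replacement of the randomized comparison. An SAP could narrow when that happens, but the stated commitment would remain.

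Several stronger readings are tempting and are not supported:

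- **That balance tests alone decide the analysis, and that the switch is about as likely as not to occur.** The rule has a second condition, so the percentages above do not measure the chance of substitution.
- **That the 5% level no longer holds.** A mechanical rule does not inflate it. Picking the best result would, but the article does not propose that; it only leaves room for it.
- **That baseline viral load is adjusted for only when p < 0.05.** Blood for viral load is drawn at baseline, 6, 12 and 15 months (Follow-up assessments and specimen banking), which matches the four repeated measures in the Power analysis. Baseline therefore appears to be in the outcome vector already, and the group-by-time term takes account of a chance difference there.
- **That marginal structural models are simply the wrong tool.** For a single treatment assigned once they reduce to weighting. Randomized arms do not need either as the main analysis.
- **That the sentence "we will confirm that there are no differences in the mean number of intervention and attention-control sessions completed" belongs to the same fault.** A non-significant test cannot confirm equality, but neither sessions nor attrition is stated to change the model.

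**Conclusion.** The point holds in this form: the article states a rule under which the comparison of randomized arms may be replaced, on a judgement that can follow sight of outcome results, and it protects no single estimate as primary. This is a rule fixed badly, not a detail left out.

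The size is moderate. With 5 to 10 independent covariates tested at 0.05 (all assumed), about 23% to 40% of perfectly randomized trials would pass the first step. How often the second step would follow cannot be calculated. Type I error would be at risk only through selective use of the discretion: in the simulation, 0.052 to 0.058 overall and 0.076 to 0.103 among flagged trials. The main cost is to interpretation, because readers could not tell which estimate had been planned. It should be corrected, and it does not undermine the design or the sample size.

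**What to change.** In Outcome analyses:

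1. Remove the significance tests of baseline equality as a decision rule, and describe the baseline table without them.
2. State that one prespecified random coefficient comparison of the arms as randomized is primary whatever the baseline table shows.
3. Fix how baseline log10 viral load enters: either in the outcome vector with the arms constrained equal at baseline, or as a covariate.
4. Name one or two prognostic covariates already collected and include them regardless of balance. Being on ART is a candidate; it is recorded at each assessment, which I take to include baseline.
5. Report propensity weighting or marginal structural models as sensitivity analyses only.

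The cost is slight: wording and some analysis work, with no new data or visits. If baseline viral load stays in the outcome vector, the power statement is untouched.

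If it becomes a covariate, three post-baseline measures remain and the statement based on four must be redone. Under the same simplifying assumptions, d = 0.5115 × √((1 + 2ρ)/3 − ρ²):

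- ρ = 0.1: 0.5115 × √0.39 = 0.319
- ρ = 1/3, the largest value: 0.5115 × √(4/9) = 0.341
- ρ = 0.8: 0.5115 × √0.2267 = 0.244

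Compared with the four-measure formula, this is slightly larger at ρ = 0.1 (0.319 against 0.292) and clearly smaller at ρ = 0.8 (0.244 against 0.472). The restatement is needed, but over this range of ρ the result stays below the upper end of the published range.

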**Methods/Design:**

This randomized controlled trial with HIV-positive, methamphetamine-using men who have sex with men (MSM) is examining the efficacy of a 5-session, individually delivered positive affect regulation intervention – Affect Regulation Treatment to Enhance Methamphetamine Intervention Success (ARTEMIS). ARTEMIS is designed to sensitize individuals to non-drug-related sources of reward as well as assist with managing depression and other symptoms of stimulant withdrawal during CM. HIV-positive, methamphetamine-using MSM who are enrolled in a community-based, 12-week CM program are randomized to receive ARTEMIS or an attention-matched control condition. Follow-up assessments are conducted at 3, 6, 12, and 15 months after enrollment in CM. Four peripheral venous blood samples are collected over the 15-month follow-up with specimen banking for planned biomarker sub-studies. The primary outcome is mean HIV viral load. Secondary outcomes include: sustained HIV viral suppression, T-helper cell count, psychological adjustment, stimulant use, and potentially amplified transmission risk behavior.

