### Follow-up assessments and specimen banking

At 3, 6, 12 and 15 months after enrollment in CM, each participant completes computer-based follow-up assessments that are administered by a trained interviewer who has not administered intervention or attention-control sessions to that participant. Self-reported substance use and sexual behavior measures are completed by participants using audio computer-assisted self-interviewing to enhance reliability and validity [51]. Urine samples for on-site toxicology testing for recent use of methamphetamine, cocaine, opiates, marijuana, and benzodiazepines (Redwood Biotech iCup®; Santa Rosa, CA) are collected at each assessment. Peripheral venous blood samples are collected at baseline as well as 6, 12, and 15 months following enrollment in CM to measure HIV viral load and CD4+ T-cell count. Participants receive a pre-loaded $50 debit card for completing each of the assessment visits over the 15-month period.

Participants are also asked to provide an additional 25 ml of peripheral venous blood using two 10 mL EDTA and two 5 mL PAXgene® tubes (Qiagen, Inc.) at baseline as well as 6, 12, and 15 months following enrollment in CM. Using EDTA tubes, leukocyte DNA is extracted and banked. Approximately three mL of plasma are also banked. PaXgene® tubes are used for isolation and stabilization of RNA. These tubes are progressively frozen and banked.

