#### Potentially amplified transmission risk behavior

Participants report the number of anal sex partners in the past 3 months, stratified by whether or not they were feeling the effects of methamphetamine [21]. The total number of condomless HIV-negative or unknown serostatus partners is calculated, stratified by methamphetamine use. Potentially amplified transmission risk partners are the number of condomless anal sex partners who are HIV-negative or unknown serostatus where participants have a HIV viral load greater than 200 copies/mL at the same assessment visit. The total number of potentially amplified transmission risk partners stratified by methamphetamine use will be calculated. We will also examine any engagement in any potentially amplified transmission risk as an outcome.

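### The planned month-3 comparisons of viral load, CD4+ count and amplified transmission risk have no data, because no blood is drawn at month 3

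*Protocol article*

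**What the plan says.** The Outcome analyses section gives the primary outcome as follows: "The primary outcome will be log_10_ HIV viral load over the 15-month follow-up". Its lead intent-to-treat analysis is a multilevel model with random intercepts and slopes, in which the arms are compared through the group-by-time interaction. It then adds visit-wise tests: "planned comparisons will be performed to test group differences at 3, 6, 12, and 15 months for both the primary and secondary outcomes". Each is to be judged at α = .05. No outcome is excepted.

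The section Follow-up assessments and specimen banking sets two different schedules.

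- Interviews, questionnaires and urine: "At 3, 6, 12 and 15 months after enrollment in CM, each participant completes computer-based follow-up assessments".
- Blood: "Peripheral venous blood samples are collected at baseline as well as 6, 12, and 15 months following enrollment in CM to measure HIV viral load". The same draws supply the CD4+ count.

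The abstract agrees with the blood schedule: "Four peripheral venous blood samples are collected over the 15-month follow-up". Viral load is assayed in plasma and CD4+ count in whole blood, so neither can come from the month-3 urine sample. The section on potentially amplified transmission risk counts a partner only "where participants have a HIV viral load greater than 200 copies/mL at the same assessment visit".

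**The concern.** The list of test visits matches the interview schedule, but it is applied to outcomes that follow the blood schedule. For those outcomes month 3 is a visit with no measurement on anyone.

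Month 3 is also a visit that readers will look at. It falls at about the end of the 12-week CM programme, and the Background recalls an earlier trial in which viral load fell immediately after CM and the gain was not maintained. A mixed model with linear time will return a month-3 estimate and p-value on request. Under the present wording, that number could be reported as a prespecified test of the primary outcome although no viral load was taken at that visit.

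**Working it through.** **1. Schedules side by side**

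| | Baseline | 3 mo | 6 mo | 12 mo | 15 mo |
|---|---|---|---|---|---|
| Planned group comparison (Outcome analyses) | – | yes | yes | yes | yes |
| Interview, questionnaires, urine | yes | yes | yes | yes | yes |
| Blood: viral load, CD4+ | yes | **no** | yes | yes | yes |

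(The baseline entry for interview and urine is taken from the baseline assessment in the run-in; nothing below depends on it.)

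Planned test visits {3, 6, 12, 15} minus post-baseline blood visits {6, 12, 15} leaves {3}. So 1 of 4 planned comparisons of log10 viral load has no observations, and 3 of 4 can be done.

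**2. Outcomes affected**

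- log10 viral load (primary).
- CD4+ count.
- Amplified-risk partners, stratified by methamphetamine use (two counts).
- Any amplified risk.

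That makes five, counting the two strata separately. Sustained viral suppression is one binary outcome over the whole 15 months and has no visit-wise comparison. Affect, depression, craving, stimulant use, urine toxicology, and ART adherence and persistence belong to the questionnaire and urine schedule, so their month-3 comparisons stand.

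**3. What the model would give at month 3**

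With time in months entered linearly, the fitted group difference at time t is β_G + β_GT × t, so at month 3 it is β_G + 3β_GT. Both coefficients are estimated from all four draws (0, 6, 12 and 15 months), and none of the information comes from month 3. The estimate is right only if the straight line is right. If time is categorical, there is no month-3 parameter for these outcomes and the contrast cannot be estimated. The article does not state the shape of time.

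**4. Does the power statement depend on a month-3 draw?**

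Inputs from the Power analysis section: 150 participants, 80% retention, four repeated viral load measures, minimum detectable d of 0.29–0.47. Assumptions not in the article: equal arms (150 × 0.8 / 2 = 60 per arm), two-sided α of 0.05, 80% power, and a common within-subject correlation ρ.

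d = (1.960 + 0.842) × √[(2/n) × (1 + (m − 1)ρ)/m]

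With n = 60 and m = 4:

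- ρ = 0.1: 2.802 × √(0.03333 × 1.3/4) = 0.29
- ρ = 0.8: 2.802 × √(0.03333 × 3.4/4) = 0.47

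This reproduces the stated range. Four measures is also the number of scheduled draws (baseline, 6, 12 and 15 months). A month-3 draw would make five, for which the same correlations give 0.27–0.47. The power statement is therefore consistent with the blood schedule and does not rely on month 3.

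**The case against.** The strongest reply is that the sentence is loose collective wording in a condensed article. Read literally, it would also call for visit-wise tests of sustained suppression, which the same section defines as a single 15-month outcome. The abstract, the blood schedule and the power statement all make clear which visits have a viral load. The lead test is the group-by-time interaction, and it can be fitted to the four draws as they stand.

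Most of this is right, and it limits the point. It does not remove it. The sentence names the primary outcome, fixes the visits and the α, and makes no exception. That is a stated analysis that the design cannot deliver, rather than detail left to an analysis plan. Nor do the missing-data methods rescue it. Maximum likelihood and multiple imputation are offered for incomplete data under a missing-at-random assumption. When nobody is measured at a visit, there are no observed values from which the distribution at that visit could be learned.

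Some stronger readings are tempting and are not supported:

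- *The primary analysis or the sample size fails.* Neither uses a month-3 viral load. The four measures in the power statement do include baseline. With only the three post-baseline values, the formula above gives 0.32–0.48, a small change, and the article does not say that the calculation was meant to leave baseline out.
- *The month-3 estimate is just an interpolation between baseline and month 6.* A linear slope uses all four draws. The sound criticism is that the estimate depends on the model and has no data at the visit.
- *A missing month-3 viral load will be coded as no risk, or imputed.* Nothing in the article proposes either. The same-visit requirement most naturally leaves the variable undefined at month 3.

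**Conclusion.** The contradiction is real and internal to the article. One of four planned comparisons of the primary outcome, together with the month-3 comparisons of CD4+ count and the amplified-risk outcomes, has no observed data by design. The consequence is narrow. The group-by-time test, the stated power, the 6-, 12- and 15-month comparisons, and the month-3 comparisons of questionnaire and urine outcomes all stand. The conclusion rests only on the two schedules as printed and on the same-visit definition of amplified risk. The assumptions in the power check bear only on showing that the stated power is untouched. It should be corrected before analysis because it concerns prespecified tests of the primary outcome.

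**What to change.** Replace the sentence on planned comparisons with one stating that they are made at each visit where the outcome is measured:

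- 6, 12 and 15 months for log10 viral load, CD4+ count and the amplified-risk outcomes;
- 3, 6, 12 and 15 months for outcomes collected at every assessment: affect, depression, craving, stimulant use, urine toxicology, and ART adherence and persistence.

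Add that no model-based or imputed month-3 viral load will be reported as a planned test. If blood is in fact collected at month 3, leave the sentence as it is for these outcomes and correct instead the abstract, the section on follow-up assessments and specimen banking, and the number of viral load measures in the power analysis.

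The first route costs one sentence and changes neither data collection nor sample size.

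### Planned visit comparisons of viral load are each tested at an unadjusted 0.05 beside the group-by-time test, with no test named as confirmatory: roughly 10–17% chance of a false positive if any of them may count as efficacy

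*Protocol article*

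**What the plan says.** All the testing rules are in the protocol article, Outcome analyses.

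- **Model.** Intent-to-treat analyses rest mainly on random coefficient models: "These models incorporate random intercepts and slopes for each participant based on the participant’s multiple measurements over time". The arms are compared "across time via the group-by-time interaction effect". No significance level is given for this test.
- **Visit comparisons.** "A priori planned comparisons will be performed to test group differences at 3, 6, 12, and 15 months for both the primary and secondary outcomes".
- **Their level.** "These planned comparisons will be evaluated at α = .05".
- **Multiplicity control.** It covers a different set of tests: "any subsequent post-hoc comparisons will be adjusted via simulation-based stepdown methods to maintain a nominal Type I error rate of .05".
- **Primary outcome.** This section describes it as log10 "HIV viral load over the 15-month follow-up". The Abstract speaks of mean viral load, and the HIV viral load subsection of change in the mean log10 value. None of the three names a time point or contrast.

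Follow-up assessments and specimen banking fixes which visit tests are possible for the primary outcome: "Peripheral venous blood samples are collected at baseline as well as 6, 12, and 15 months following enrollment in CM to measure HIV viral load". There is no draw at 3 months.

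**The concern.** The primary outcome has several routes to a nominally significant result: the interaction, and a comparison at each visit with a viral load. The text does not rank them and does not make the visit tests depend on the interaction.

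Calling the visit tests planned prevents their being chosen after the data are seen. It does not limit the chance that at least one of several tests is positive when there is no effect. The plan recognises multiplicity, since it adjusts post-hoc tests, but it exempts the tests most likely to carry the main conclusion.

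At stake is how a mixed result would be read. Suppose there is a difference at 12 months only, with a flat interaction. Under this text it would be a planned, significant finding on the primary outcome, and a reader could not tell whether the trial had met its objective.

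**Working it through.** **Step 1. Inputs.**

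- From Power analysis: total N = 150, 80% retention (150 × 0.80 = 120), four repeated measures, detectable d = 0.29–0.47.
- From Outcome analyses: α = .05 for each planned visit comparison.
- From Follow-up assessments: viral load at months 0, 6, 12 and 15, so three post-baseline visit tests.
- Assumed because not stated: two-sided tests, 80% power, .05 for the interaction, and the within-subject correlation ρ.

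**Step 2. Reproduce the plan's own figure.** For a time-averaged two-arm difference under compound symmetry,

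d = (1.960 + 0.842) × √[(4/N) × (1 + (m − 1)ρ)/m], with N = 120 and m = 4.

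- ρ = 0.1: 2.802 × √(0.03333 × 0.325) = 0.292
- ρ = 0.8: 2.802 × √(0.03333 × 0.850) = 0.472

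This matches 0.29–0.47; N = 150 gives 0.26–0.42 over the same ρ and does not. Two things follow. A ρ of 0.1–0.8 is a reasonable working range. And the contrast that reproduces the stated effect sizes is the time-averaged difference, which is neither the interaction nor a single-visit test. So the power section does not settle which test is primary.

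**Step 3. Reference values under independence.** Three tests: 1 − 0.95³ = 14.3%. Four tests: 1 − 0.95⁴ = 18.5%. The tests here are correlated, so the actual values must be simulated.

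**Step 4. Simulation under no effect at any visit.** 500,000 draws of the between-arm differences at months 0, 6, 12 and 15. A false positive is any two-sided rejection at 0.05. Compound symmetry, values for ρ = 0.1 → ρ = 0.8:

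| How the visit contrasts are built | Three visits alone | Plus linear interaction (1 df) | Plus interaction with time as categories (3 df) |
|---|---|---|---|
| Free visit means | 14.2% → 9.8% | 17.3% → 14.1% | 15.7% → 13.7% |
| Baseline-adjusted | 14.2% → 12.9% | 17.1% → 14.4% | 15.5% → 13.9% |
| Change from baseline | 12.5% → 12.5% | 13.4% → 13.4% | 13.5% → 13.5% |
| From a fitted linear trajectory | 9.6% → 6.7% | 12.4% → 11.1% | 13.3% → 11.2% |

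**Step 5. Other covariance structures.** Results for three visits plus the linear interaction:

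- Autoregressive, correlation 0.5–0.9 per 6 months: 15.3% → 12.5% (free means), 11.2% → 10.3% (change), 12.2% → 11.3% (linear trajectory).
- Random intercept and slope (assumed intercept variance 0.6, residual variance 0.4, slope adding 0.3–1.0 to the variance at month 15): 15.1% → 13.8% (free means), 12.8% → 11.7% (change), 11.4% → 10.8% (linear trajectory).

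With the interaction included, the results run from about 10% to 17%, always at least twice 5%. Without it, the three visit tests alone give about 7–14%.

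**Step 6. After a fix.** With one primary test at 0.05 and the visit tests gated behind it, no claim is possible unless that test rejects, so the error when there is no effect at all is 5%. The alternative is Bonferroni over four tests at 0.05/4 = 0.0125. That replaces 1.960 by 2.498 in Step 2 and raises the detectable d to 0.292 × 3.340/2.802 ≈ 0.35 and 0.472 × 3.340/2.802 ≈ 0.56.

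**The case against.** The other side has four arguments.

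1. **Size.** The plan specifies random intercepts and slopes and compares trajectories. If the visit contrasts come from a fitted linear trajectory, the inflation is 11–12% under compound symmetry, not 14–17%. This stands. A reader might take 14–17% as the size of the problem, but it is the upper part of a range. The article gives no correlation, no coding of time and no construction of the visit contrasts.

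2. **What the text promises.** A reader might infer that the plan sets 0.05 for the interaction, or that it guarantees a 5% overall rate for the primary outcome and breaks it. Neither is written. The .05 is attached to the planned visit comparisons, and the only promise to hold a Type I error rate concerns post-hoc tests. This also stands, which is why the interaction's level is listed as an assumption. The visit tests alone still exceed 5%.

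3. **How results would be used.** Nothing says that one significant visit will count as efficacy, and the trajectory comparison can be read as the main test. That is a fair reading, but the text does not fix it, and the power figures point to a third contrast. The inflation is therefore conditional on how the results are read.

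4. **An unseen analysis plan.** A hierarchy could be set there. That would answer a silent protocol. This one states an unadjusted level for the planned tests and limits adjustment to others, so a hierarchy elsewhere would have to depart from it.

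A reader might also count a fourth visit test, or five tests in all (1 − 0.95⁵ = 22.6% if independent). No viral load is drawn at 3 months and the tests are correlated, so that overstates the error. Nor are many unadjusted secondary tests a defect in themselves in a Phase II trial, provided they are labelled as such.

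**Conclusion.** The point holds as a stated rule, not as an omission. The plan tests the primary outcome several times, fixes the visit tests at an unadjusted .05, and designates none of the tests as confirmatory.

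If a positive result on any one may be read as efficacy, the chance of at least one false positive is roughly 10–17%. That rests on two-sided tests, .05 for the interaction, three visit tests, and the assumed correlations and covariance structures. The direction is secure, but the exact size is not.

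It should be fixed. It does not invalidate the trial: this is a Phase II study, no overall error rate was promised for the primary outcome, and the remedy needs no new data.

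**What to change.** Before outcome data are unblinded, amend the Outcome analyses wording as follows.

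- Name one primary test of log10 viral load at two-sided 0.05. The simplest choice is the group-by-time test already planned. The time-averaged difference is the alternative, being the contrast that reproduces the stated effect sizes if 80% power is assumed; choosing it changes the planned contrast and should be recorded as such.
- Test the 6-, 12- and 15-month contrasts only if the primary test is significant, using the step-down method the plan already has. Otherwise label them supportive.
- Remove the 3-month comparison for viral load, or state that it applies only to outcomes measured then.
- Label secondary-outcome p-values as unadjusted.

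The cost is wording, plus one real restriction: an isolated effect at a single visit can no longer be claimed as efficacy. The primary test keeps its full 0.05, so it loses no power, unlike Bonferroni over four tests, which would move the detectable d from 0.29–0.47 to about 0.35–0.56.
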